### External and subgroup validation

While model development and internal validation will be performed using data from a single clinical centre, further validation is planned at a second site of our hospital that predominantly treats gynaecological and ENT patients. This cohort will serve as a distinct population for assessing model generalisability across surgical disciplines.

Additionally, the model will be evaluated in a separate high-risk subgroup comprising patients undergoing urgent or emergency procedures, such as elderly individuals with hip fractures. These patients were intentionally excluded from the initial development cohort and will offer insight into the model’s performance in more acute care settings.

### Interim analysis

An interim analysis will be conducted after the enrollment of approximately 50 patients (around 10% of the planned sample size). This analysis will assess the technical feasibility, data quality, and operational workflow. As this is a non-interventional study, early termination is not planned regardless of interim results.

### Oversight and monitoring

The Coordinating investigators are responsible for study design, funding, and creation of the study protocol. They take over the coordination and communication between the two involved departments, the Department of Anaesthesiology and Intensive Care Medicine and the Department of Radiology, and the persons involved in the study. Furthermore, they are part of the trial steering committee.

The trial steering committee is responsible for adhering to the study protocol, conducting the planned patient enrollment, and compiling the patient identification list. They will monitor the study’s progress and, if necessary, agree on changes to the procedure and study protocol. The committee meets once every 2 months in an in-person or online meeting.

The Lead investigator is responsible for eligibility, consent, and enrollment of patients as well as imaging and data collection, and therefore supports the practising physicians on a day-to-day basis.

The present study is not a study according to the German Medical Product Act (AMG) or the Medical Devices Regulation (MDR). The study is monocentric, and no intervention will take place. No risks for the patients are to be expected. For these reasons, no external data monitoring committee will be set up.

However, the coordinating investigators will be responsible for the creation of the database, supporting data entry, data verification, and quality management. Data monitoring and outcome reports will take place every 8 weeks.

### Adverse events and harms

Patients will undergo routine perioperative care as per standard during this trial; responsible for patient care will be the attending physicians and departments. Additionally, patients will receive (1) a lung ultrasound, considered non-invasive and without side effects, and (2) a clinical examination and interview at up to three time points postoperatively. All other procedures are part of general anaesthesia or usual perioperative management and are completed even without study participation. Therefore, we do not expect any complications or harm from trial participation.

Nevertheless, patients can report adverse events or other unintended effects of the trial to the study hotline or email address. The trial steering committee will process the reports.

Due to the relatively small size of the data set, the prediction model will be developed using the whole dataset. Cross-validation will be used to evaluate the performance of the model. Furthermore, validation is planned on a temporally independent data set obtained during the period of model training. Therefore, the study will be classified as Type 1b according to the TRIPOD Statement [12].

Error analysis will be carried out with the help of a confusion matrix after threshold determination. The cases of incorrect predictions will be analyzed in more detail, in particular, to determine whether certain characteristics correlate with the errors. External validation will take place in future studies.

In the current study, we are not focusing on the identification of possible confounders for model performance. This will be done in a follow-up study, investigating the impact of possible confounders such as different raters, imaging devices, bad image quality, resolutions, etc., in a possibly multi-centric study.

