### Three predictive models will be developed

First, a model based on deep learning using lung ultrasound images, second, a model based solely on clinical variables using common frameworks like automated machine learning (AutoML), and finally, a combined model integrating both clinical and imaging features.

The dataset will be split using stratified, patient-wise sampling into non-overlapping training and hold-out test sets. Internal model performance will be assessed using k-fold cross-validation within the training set, and final evaluation will be conducted on the independent test set. Full details of the modelling and validation procedures are provided in the statistical methods.

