### Overview of modelling approaches

Three predictive modelling strategies will be pursued. First, an imaging model will be created using deep learning techniques applied to lung ultrasound images. This model will be developed in Python using the PyTorch framework. Transfer learning will be employed, utilizing pretrained convolutional neural network (CNN) architectures such as ResNet or DenseNet. These models will be fine-tuned on the study-specific dataset. We will also assess the performance of medical foundation models and contrastive learning-based pretraining to optimize feature extraction from the ultrasound images.

Second, a clinical model will be developed using only structured patient data. This model will be trained using frameworks like H2O AutoML within R/RStudio as well as built-in R functions, which allows for the systematic evaluation and tuning of various machine learning algorithms, including gradient boosting machines, random forests, and neural networks.

Third, a combined model will integrate both clinical and imaging data. Various fusion strategies will be explored, including early and late fusion, to determine the most effective method for combining heterogeneous data types. The final architecture for this combined model will be selected based on performance observed in a hold-out test dataset.

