### Missing values and data imputation

With regard to imaging data, only complete data sets will be accepted for analysis.

Missing values in the clinical dataset will initially be handled using the default preprocessing pipeline in the case that H2O AutoML is used. This pipeline applies median or mean imputation for numerical variables and mode imputation for categorical variables (https://docs.h2o.ai/h2o/latest-stable/h2o-docs/data-munging/imputing-data.html). In addition to this standard approach, we will evaluate alternative imputation strategies, particularly for approximately normally distributed numerical variables. These include, e.g., k-nearest neighbors (kNN) imputation, which leverages similarities across observations in the multivariate feature space and multiple imputation using chained equations (MICE), which incorporates multivariable relationships and reflects the uncertainty associated with imputed values.

Given the prospective nature of the study, we anticipate that most missing data will not be missing at random (NMAR), but rather occur systematically, for instance, due to early patient discharge or an inability to perform assessments as a result of clinical deterioration. In such cases, the absence of data may itself be informative with respect to the patient’s risk for postoperative complications. Therefore, in addition to the imputation techniques mentioned above, we will explore modelling strategies that explicitly account for informative missingness. These include the incorporation of missingness indicators (binary flags denoting whether a variable was observed or missing) and sensitivity analyses to assess the robustness of model predictions under different assumptions about the missing data mechanism.

The final approach to handling missing data will be selected based on a combination of model performance, diagnostic checks, and clinical plausibility.

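### The cross-validated AUROC will be optimistic, because algorithm, tuning and imputation are chosen on the same cohort that is cross-validated

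*Protocol article*

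**What the plan says.** All places are in the protocol article.

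- **Adverse events and harms** (closing text on model development). Because the data set is small, "the prediction model will be developed using the whole dataset", and "Cross-validation will be used to evaluate the performance of the model". The next sentence adds that "validation is planned on a temporally independent data set obtained during the period of model training". The paragraph concludes that "the study will be classified as Type 1b according to the TRIPOD Statement".
- **Three predictive models will be developed.** "Internal model performance will be assessed using k-fold cross-validation within the training set, and final evaluation will be conducted on the independent test set".
- **Overview of modelling approaches.** The clinical model uses AutoML-type frameworks, which permit "systematic evaluation and tuning of various machine learning algorithms". The data on which the winner is picked are not named. The architecture of the combined model is chosen by its performance on a hold-out test dataset.
- **Missing values and data imputation.** Several imputation methods and missingness indicators are candidates. "The final approach to handling missing data will be selected based on a combination of model performance", together with diagnostic checks and clinical plausibility. Again the data used are not named.
- **Model training and evaluation.** Architecture and hyperparameters are optimised by hold-out validation inside the training data. K-fold cross-validation is there to assess robustness and limit overfitting. The imaging model mainly uses a fixed split. Final evaluation, including AUROC, is on newly enrolled patients outside the training data.

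**The concern.** When the best of several candidates is picked on a set of patients, part of its lead is chance. Cross-validation protects against overfitting of the model fitted within each fold. It does not protect against choices that have already used all folds. To cover those, the choices must be repeated inside each training part, or made before the cross-validation on other data.

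The whole-dataset wording leaves no other data within the cohort. A hold-out portion used for tuning in early experiments belongs to the same cohort, so those patients return in the folds that give the performance figure.

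ARISCAT has fixed published weights and gains nothing from such choices. The optimism therefore falls on the machine-learning side only. It matters because the main hypothesis is that the algorithm outperforms clinical scores, and the sample size section asks for a significant improvement at the 0.05 level.

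**Working it through.** The plan gives no figure for this bias, so there is none to reproduce. The sample size of 512 serves only as an input. It cannot be reproduced uniquely, since the event rate, the correlation between the two AUROCs and the sidedness are not stated for it, and it does not decide this point.

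**Inputs from the article.** 512 patients; reference AUROC 0.83 and target 0.93 (Sample size); complication rate 111/259 = 43% (Addressing overfitting and class imbalance). Hence about 0.43 × 512 = 220 patients with and 292 without a complication.

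**Assumptions.** K = 5 to 50 candidate pipelines with equal true AUROC; correlation r = 0.5 to 0.9 between their AUROC estimates. The article gives neither.

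**Step 1: standard error of one AUROC (Hanley–McNeil).** The variance is [A(1−A) + (nD−1)(A/(2−A) − A²) + (nN−1)(2A²/(1+A) − A²)] / (nD·nN), with nD·nN = 220 × 292 = 64,240.

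- A = 0.83: (0.1411 + 219 × 0.02050 + 291 × 0.06400) / 64,240 = 0.000362, so SE = 0.0190.
- A = 0.93: (0.0651 + 219 × 0.00426 + 291 × 0.03137) / 64,240 = 0.000158, so SE = 0.0126.

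**Step 2: expected excess of the best of K.** For equicorrelated, approximately normal estimates it is SE × √(1−r) × m(K). Here m(K) is the expected maximum of K independent standard normal values: m(5) = 1.163, m(50) = 2.249.

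| True AUROC | K = 5, r = 0.9 | K = 50, r = 0.5 |
|---|---|---|
| 0.93 | 0.0126 × 0.316 × 1.163 = 0.005 | 0.0126 × 0.707 × 2.249 = 0.020 |
| 0.83 | 0.0190 × 0.316 × 1.163 = 0.007 | 0.0190 × 0.707 × 2.249 = 0.030 |

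The range is therefore about 0.005 to 0.03. The planned difference is 0.93 − 0.83 = 0.10.

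**Step 3: what this would do to a test against ARISCAT.** The setting was simulated twice, with 600 and 800 replicates per setting: 512 patients, 43% events, ARISCAT and all candidates at a true AUROC of 0.83, and a DeLong test of the best candidate against ARISCAT. Scores within an outcome class were assumed to correlate 0.5 to 0.85 among candidates and 0.5 with ARISCAT. False superiority, against a nominal 2.5% in that direction, was:

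- one candidate: about 2% to 3%;
- best of 5: 6% to 8%;
- best of 20: 9.5% to 25% in one run and 10.5% to 21% in the other;
- best of 50: 15% to 33% in one run and 15% to 30% in the other.

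The simulation picks the best of K scores and does not run a full cross-validation. It shows how the selection works but does not forecast this study's error rate.

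**Step 4: new patients.** On patients who played no part in any choice, the selection excess is zero by construction.

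**The case against.** A reader might infer that the trial's reported AUROC, and with it the claimed superiority over ARISCAT, is biased upward. The documents do not support that. Two sections place the final evaluation, AUROC included, on independent patients, and the sentence directly after the one on cross-validation adds a temporally separate data set. Nor does any section say that ARISCAT will be tested against cross-validated predictions.

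A reader might also infer that cross-validation is the stated tool for choosing the model. It is not. The tool named for architecture and hyperparameters is hold-out validation within the training data, and imputation is judged on diagnostics and plausibility as well as performance. The imaging model of the primary objective mostly uses a fixed split, so the point bears chiefly on the clinical model and on any other model that is cross-validated. The analysis plan, a supplement not seen here, may also specify nesting.

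These objections narrow the point but do not remove it. The article still names cross-validation on the whole dataset as a performance evaluation and ties the study's TRIPOD type to that paragraph. Whichever device does the choosing, it draws on the same cohort. Nor is the independent set fully secured: it has no stated size, one section describes it as a split of the dataset and another as later enrolment, and the combined architecture is chosen on a hold-out test dataset. If that is the same set, its result would carry a selection excess of its own.

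**Conclusion.** The point holds for the cross-validated estimate. As written, the cross-validated AUROC of the selected model, and any comparison with ARISCAT built on it, would be optimistic by roughly 0.005 to 0.03. The size rests on assumed numbers of candidates (5 to 50), equal true performance among them, correlations of 0.5 to 0.9 between their AUROC estimates, and the 43% event rate of the preliminary study. The excess is small beside the planned difference of 0.10 and could not create such a gain. It could, however, inflate a significance test when the true difference is small. The final evaluation on newly enrolled patients is not affected, on the condition that nothing is selected on that set.

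**What to change.** Amend three places: Three predictive models will be developed, Model training and evaluation, and the model-development text under Adverse events and harms.

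1. State that every data-driven choice (algorithm, hyperparameters, imputation method) is made in an inner loop, and that cross-validated performance is reported from the outer folds only.
2. Where repeating this is too costly for the image network, fix its pipeline before the outer evaluation starts.
3. Score ARISCAT on the same outer-fold patients.
4. Label the cross-validated result as internal validation, and base the superiority conclusion on the temporal hold-out set, left untouched until all models, including the fusion architecture, are fixed.

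The cost is wording, more computing time and a slightly less favourable cross-validated AUROC. The nesting itself needs no additional patients.

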**Fig 2 pone.0329076.g002:**
[figure not shown]
Graphic representation of the lung ultrasound areas. Lung ultrasound will be performed in 12 areas, 6 in each hemithorax. Areas are separated by the anterior and posterior axillary line into an anterior, lateral and posterior zone and a superior and inferior area.

The criteria for including imaging data are described above (“Eligibility Criteria”). If these conditions are not met, the interpretability of the ultrasound is considered insufficient.

To maximize inclusiveness and minimize selection bias, operators are encouraged to adjust technical parameters (e.g., depth and gain) during image acquisition in order to meet these quality criteria. A convex transducer was selected to allow visualization of deeper structures across a wide range of patient anatomies.

The performing physicians are experienced in perioperative medicine and critical care and will be trained in ultrasound methodology before the start of the study.

After transmission and storage in the PACS of the Department of Radiology, image pre-processing and artifact correction are performed before the data serves as input for the machine learning model. Images are not labeled by human experts; only the pre-defined endpoint POPC serves as labels for the imaging data.

The clinical data obtained for the study correspond to parameters routinely collected during anesthesiologic preoperative evaluation, the course of anaesthesia during surgery, and postoperatively in the recovery room. Plausibility checks are carried out on the numerical data; if these deviate from the valid value range, they are removed. Missing data may be imputed by different methods as described below.

Based on the collected data and the outcome parameters (description in chapter “Outcome”), machine learning algorithms will be trained to predict POPC by outputting an individual patient’s percentage risk of suffering a postoperative pulmonary complication.

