### Sample size

Predicting POPC for the clinician is difficult on a case-by-case basis. Therefore, several scoring systems have been developed in the past. The most common of these, the ARISCAT score, has an AUROC of 0.83 [15]. It should be noted that the current literature does not provide any further metrics such as area under the precision-recall curve (AUPRC) or F1 score on the ARISCAT [15,16]. We therefore used the AUROC as the reference metric. The model we aim to create should be significantly better than the ARISCAT score and thus have at least an AUROC of 0.93. Achieving this seems realistic since, in the preliminary work of our research group, prediction models for various postoperative complications have already been created, whose predictive accuracy is in this range [17,18]. With a significance level of 0.05 and a power of 80%, 512 patients would be needed to create the database based on the method described by Hanley and McNeil for comparing ROC curves [19].

Patients are stratified according to the risk criteria determined by ARISCAT so that approximately equal numbers of patients are included in each of the low-risk (ARISCAT < 26 points), intermediate-risk (ARISCAT 26–44 points), and high-risk (ARISCAT ≥ 45 points) groups.

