### Model training and evaluation

The primary model development will be based on a dataset of 512 patients. Within this cohort, we will implement stratified k-fold cross-validation (typically 5- or 10-fold, depending on the final class distribution) where possible to assess model robustness and mitigate overfitting. Image-based deep learning models require extensive computational resources, therefore, cross-validation will be applied more selectively. We will therefore use a fixed training/validation/test split for imaging data, ensuring non-overlapping patient groups. Early model experiments will be conducted using internal validation on the training data with hold-out validation to optimize architecture and hyperparameters. Final model evaluation will be performed on an independent hold-out test set.

This hold-out test set will be compiled prospectively during the course of the study after model development, using newly enrolled patients not included in the training dataset. This temporal separation will ensure unbiased performance evaluation of the final model.

Model performance will be evaluated on the independent hold-out test set using several complementary performance metrics. These will include the area under the receiver operating characteristic curve (AUROC), the area under the precision-recall curve (AUPRC), overall accuracy, sensitivity, specificity, F1-score, as well as positive and negative predictive values. Calibration will be assessed using appropriate measures, such as the Brier score, Hosmer-Lemeshaw-Test and calibration curves. Clinical decision-making utility can additionally be evaluated using decision curve analysis (DCA).

Importantly, our models are designed to output individualized risk probabilities, not dichotomous predictions. As such, the selection of a cut-off point for potential clinical decision-making will be a post-modelling step, and risk thresholds for high-risk patient classification will not be predefined. Instead, various thresholding strategies will be explored post hoc, including Youden’s index (for balanced sensitivity and specificity), cut-offs optimized for specific clinical priorities (e.g., maximizing sensitivity), and thresholds guided by DCA.

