### Addressing overfitting and class imbalance

Overfitting will be addressed through the implementation of several regularization techniques commonly used in deep learning. These include dropout layers within the network architecture, L2 weight regularization to penalize large weights, and data augmentation techniques applied to ultrasound images (e.g., rotation, flipping, and zooming). Model complexity will also be restricted as needed.

To better estimate the prevalence and clinical relevance of POPC, we conducted a preliminary single-center observational study involving 259 patients undergoing surgery under general anesthesia. The cohort included 106 female patients (41%) and 62 current smokers (24%) with a median age of 66 years. Overall, 111 patients (43%) experienced at least one POPC, indicating that POPC is a relatively frequent complication in the targeted patient population [25].

Based on this preliminary observational data, only moderate class imbalance is to be expected. Nevertheless, additional strategies will be employed to ensure balanced learning. These include maintaining class ratios across cross-validation folds, monitoring class-wise performance metrics, and using class weighting techniques if imbalances are observed in specific subgroups.

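### Correlating patient characteristics with misclassification at a cut-off mixes predictors of risk with real model failure; subgroup calibration would separate the two

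*Protocol article*

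**What the plan says.** Under Model training and evaluation, the protocol article states that "our models are designed to output individualized risk probabilities, not dichotomous predictions". Study measures says the same of the output, an individual patient's "percentage risk of suffering a postoperative pulmonary complication". The cut-off is left for later: "risk thresholds for high-risk patient classification will not be predefined", with Youden's index, sensitivity-driven cut-offs and decision curve analysis to be explored post hoc.

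The statistical paragraphs under Adverse events and harms then plan that "Error analysis will be carried out with the help of a confusion matrix after threshold determination", and continue: "The cases of incorrect predictions will be analyzed in more detail, in particular, to determine whether certain characteristics correlate with the errors". No test or comparison group is named for this search.

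Calibration is planned under Model training and evaluation: "Calibration will be assessed using appropriate measures, such as the Brier score, Hosmer-Lemeshaw-Test and calibration curves". As described there, these checks are for the model as a whole; no breakdown by patient characteristic is given.

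**The concern.** An incorrect prediction exists here only because a probability has been cut at a threshold. A patient given a 40% risk who develops a complication has not been predicted wrongly, yet counts as an error at any cut-off above 40%. How often this happens depends on where the patient's risk lies relative to the cut-off, and so on the variables that determine that risk.

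A search for characteristics that correlate with such errors can therefore return the model's own risk predictors and present them as weaknesses. A group in which the model really over- or under-predicts would appear in the same list, and the analysis offers no way to tell the two apart. What is at stake is how the error analysis is read, and any model revision based on it. The performance estimates are not affected.

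**Working it through.** **Inputs from the protocol article.** Prevalence: "Overall, 111 patients (43%) experienced at least one POPC" in the preliminary cohort. Reference score: ARISCAT "has an AUROC of 0.83"; target AUROC 0.93. Sample size 512, in three ARISCAT groups of about equal size (Sample size section). The article states no figure for the error analysis, so there is none to reproduce.

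**Assumptions.** Cut-offs, model coefficients, and an evaluation set of about 102 patients (20% of 512).

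**Step 1: the identity.** Take a perfectly calibrated model with risk r and cut-off t.
- If r < t, the patient is called negative and is an error when the event occurs: P(error) = r.
- If r ≥ t, the patient is called positive and is an error when no event occurs: P(error) = 1 − r.

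Error frequency is a function of r alone, so a variable that moves r generally moves the error rate.

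**Step 2: errors expected with no fault.** For an equal-variance binormal score at the Youden cut-off, the error rate is Φ(−Φ⁻¹(AUROC)/√2).
- AUROC 0.93: Φ(−1.476/1.414) = Φ(−1.044) = 14.8%, or 76 of 512.
- AUROC 0.83: Φ(−0.954/1.414) = Φ(−0.675) = 25.0%, or 128 of 512.

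**Step 3: error by risk stratum in a faultless model.** Outcomes were drawn from the model's own risks, with prevalence 43% and three equal strata. Risk varied within strata, and the Youden cut-off was used.

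| | Low | Middle | High |
|---|---|---|---|
| AUROC about 0.84 (cut-off 0.44): all errors | 0.195 | 0.276 | 0.258 |
| false negatives among events | 0.58 | 0.30 | 0.10 |
| false positives among non-events | 0.08 | 0.26 | 0.53 |
| AUROC about 0.94 (cut-off 0.43): all errors | 0.117 | 0.157 | 0.149 |
| false negatives among events | 0.27 | 0.16 | 0.08 |
| false positives among non-events | 0.07 | 0.16 | 0.28 |

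Mean predicted and observed risk agree in every stratum (about 0.23, 0.42 and 0.64 for both), so nothing is wrong with the model. Over cut-offs of 0.20, Youden and 0.50, a chi-squared test of overall error by stratum at n = 512 rejected in 31-36% of samples at AUROC about 0.84 and in 14-17% at about 0.94. At n = 102 it rejected in 5-10%. A test of outcome minus predicted risk by stratum rejected in about 4-6%.

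**Step 4: a given continuous predictor.** Perfect model, five standard normal predictors, prevalence 43%, cut-off 0.43, AUROC about 0.79 to 0.92. Share of datasets with p < 0.05:

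| Comparison | n = 512 | n = 102 |
|---|---|---|
| False positives v true negatives | 94-100% | 30-64% |
| False negatives v true positives | 85-99% | 24-50% |
| All errors v all correct predictions | 11-17% | 5-7% |
| Residual (outcome − predicted risk) | 3-5% | 3-5% |

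The ranges cover repeated runs and different predictor strengths. The cell-by-cell contrast is strong because false positives have a higher predicted risk than true negatives by definition.

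**The case against.** **The two sections do not conflict.** A reader might infer that the error analysis contradicts the statement that the output is a probability. It does not. Both sections place the cut-off after modelling, and the Objectives include finding a risk threshold for intervention. Asking who is missed or over-called at that threshold is a legitimate descriptive question, and calibration alone does not answer it. This objection stands.

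**The closest reading of the text gives a small artefact.** The protocol speaks of errors in general and names no contrast between cells of the confusion matrix. Pooled errors against correct predictions give 11-17% at 512 patients and near-nominal rates at about 100. This stands and limits the size. It does not remove the point: an ordinary reading of a confusion matrix separates false positives from false negatives, and nothing in the text prevents that.

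**A steeper illustration is tempting but unsuitable.** Suppose each third had a single true risk of 15%, 40% or 75%. Error rates would be 15%, 40% and 25%, with chi-squared 27.6 on 2 df at n = 512. But a model that knows only the third has an AUROC of about 0.77, below both the 0.83 and the 0.93 in the Sample size section. At n = 102 the statistic is 5.5, short of the 5% critical value of 5.99. It overstates the gradient.

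**The step is not blind to real faults.** A reader might infer that it can never detect miscalibration. In a simulation with an assumed 30% subgroup whose log-odds were under-predicted by 1.5 (cut-off 0.43), false-negative rates were 34% against 21%. A test among events rejected in 65% of datasets of 512, against 5% without miscalibration. The method detects such a fault but cannot separate it from the artefact.

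**The follow-up study is not shown to be misdirected.** The article already names its targets (raters, devices, image quality, resolution) and does not derive them from this step.

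**The analysis plan in S3 File is not shown** and may set out the comparisons or add calibration by subgroup. The point therefore concerns the method the article states, not the absence of detail.

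**Conclusion.** The point holds as a limited one. The stated method looks for model weaknesses through threshold-based misclassification, which depends on predicted risk even in a perfectly calibrated model. Risk predictors can therefore appear as correlates of error. The effect is strong when false positives or false negatives are taken separately. It is modest when errors are pooled for a given predictor, although for a strong risk stratum at AUROC about 0.84 the pooled rejection rate reached 31-36% at n = 512. It is small in an evaluation set of about 100.

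The identity in step 1 needs no assumption beyond calibration. The percentages rest on the assumed coefficients, cut-offs and test-set size. A characteristic unrelated to risk, or one whose effects above and below the cut-off cancel, need not show a link.

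The analysis is exploratory and alters no primary performance estimate. The documents do not support saying that it will necessarily report false weaknesses or that it must be dropped. They support a cheap improvement.

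**What to change.** In the error-analysis paragraph, and in the analysis plan if it repeats it:

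1. Keep the confusion matrix and the review of misclassified cases as description at the chosen threshold.
2. Base any statement that the model fails in patients with a given characteristic on subgroup calibration in the evaluation data: observed minus mean predicted risk, or the O/E ratio, with a 95% CI, by ARISCAT group, sex, age group and surgical discipline.

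Comparisons by rater or imaging device can stay with the follow-up study to which the article assigns them.

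Cost: a change of wording and a little more analysis on data already collected, with no new patients. Intervals will be wide in small subgroups, particularly with an evaluation set of about 100, and should be reported as such.
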